### Data collection

Table 4 gives an overview of the different measurements and time points during the study.

**Table 4 Tab4:** Measurements and time points

Parameter	Measurement method	Measurement moment		
		**Baseline**	**Post -intervention (3 months)**	**Post follow -up (3 months)**
**Metabolic indicators**				
Fasting blood glucose	CardioChek plus	X	X	X
Total cholesterol		X	X	X
HDL cholesterol		X	X	X
Triglycerides		X	X	X
Blood pressure	Seca b12 (twice)	X	X	X
Body composition	Body-stat 1500 lite touch	X	X	X
**Anthropometric**				
Weight	Weighing scale (Seca 874 dr) (twice)	X	X	X
Height	Seca height board (twice)	X		
Waist circumference	Tape (twice)	X	X	X
**Fruit and vegetable intake, food literacy and physical activity**				
Fruit and vegetable intake	Fruit and vegetable intake screener adapted from NIH screeners (https://epi.grants.cancer.gov/diet/screeners/fruitveg/instrument.html) , Additional file 9 Food literacy questionnaire (developed by our research team for Ugandan context in consideration of Poelman, Dijkstra [29] and Vidgen HA [27]. We are currently validating the questionnaire, Additional file 10	X	X	X
Food literacy		X	X	X
Physical activity (self-reported)	Short version of International Physical Activity Questionnaire (IPAQ-SF)	X	X	X
**Process indictors**				
Adherence to the programme	Attendance list		X	X
**Socio-demographic data**	Questionnaire	X		

### Data analysis

Data will be analysed using R software. To evaluate the effects of the intervention, multilevel analysis will be used. Using this technique, regression coefficients will be adjusted for the clustering of observations within sub parishes. We will define two levels in our multi-level analysis: (1) participant and (2) sub parishes. Linear mixed effect models will be used to examine the effect of the intervention on each of the outcome values. All analyses will be performed according to the intention-to treat-principle [42]. To assess changes in metabolic health between the intervention and control groups, a linear mixed effect model will be built where “time” (end line measurement (M_2_) will be compared with base-line measurement (M_1_) and post-follow up measurement (M_3_)), treatment (and interaction of time and treatment) as well as age will be specified as fixed effects, and sub parishes and participants as random factors. For all linear mixed models, compatibility with mixed-model assumptions will be checked by inspection of residual plots and Q-Q plots. In the case of heteroscedastic residuals, data will be log transformed. Tukey or Benjamini–Hochberg procedures will be applied when performing post hoc analyses to further identify differences within treatments as well as between time points. Statistical outliers will be defined as any observation which has an absolute residual exceeding 3 times the residual standard deviation. p < 0.05 will be considered significant in all analyses.

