### Step VI: Development of an evaluation plan

#### Study design, setting and timing

The effectiveness of the intervention will be evaluated through a cluster-randomized controlled trial. The intervention will be evaluated in Kampala, the capital city of Uganda. The six sub parishes of Mbuya catholic parish will be randomized to treatment and control arms, Fig. 4. The treatment arm will be exposed to both the developed intervention infographics and face to face group sessions while the control arm will only receive the developed intervention infographics. An awareness session will be organized to distribute the infographics to the control arm. Within the sub parishes, there are existing women groups. These existing groups will be utilized for face-to-face intervention group sessions. For the intervention purposes, each group will be limited to a maximum of 14 members. The study period is divided into two phases: a three-month intervention and a three-month post-intervention follow-up phase.

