### Sample size calculation

Sample size calculation is based on waist circumference.

To calculate the sample size, we used the formula described by Rutterford, Copas [40], Table 3.

**Table 3 Tab3:** Description of sample size calculation

$$\boldsymbol{m}=\frac{{\left({\boldsymbol{Z}}_{\mathbf{1}-\boldsymbol{\alpha} /\mathbf{2}}+{\boldsymbol{Z}}_{\mathbf{1}-\boldsymbol{\beta}}\right)}^{\mathbf{2}}\ \mathbf{2}{\boldsymbol{\sigma}}^{\mathbf{2}}}{{\boldsymbol{\Delta}}^{\mathbf{2}}}\left(\mathbf{1}+\left(\boldsymbol{n}-\mathbf{1}\right)\boldsymbol{\rho} \right)$$	
where? m = sample size per study arm	= 1.96 at the type 1 error of 5% = 0.842 at 80% power
σ = the standard deviation of primary outcome in the population	• Based on Uganda STEP survey [2], the standard deviation of waist circumference for women aged 18 to 49 years = 13.73.
△ = effect size = 7.4cm.	• Effect size was calculated based on Bendall, Mayr [41] , impact of the Mediterranean diet on central obesity. • Only studies with a duration below 12 months were included in the calculation as the proposed study duration is below 12 months.
(1 + (*n* − 1)*ρ*)= design effect (DE) to compensate for cluster randomisation. ▪ n = number of individuals per cluster ▪ ρ = Intra-Cluster Correlation coefficient	• For our intervention, n = 27 • ρ = 0.001 ▪ There is no data available on the intra-Cluster Correlation coefficient of waist circumference across villages for communities within Kampala. A range of 0.001 to 0.10 is demonstrated as a cost - effective and safe choice to account for the variability.

m = (1.96 + 0.842)^2^ *2*13.73^2^/7.4^2^) * (1 + (27-1) *0.001)

m = 55 participants

To cover for dropouts, m is increased by 20%, to make 66 participants.

Hence, the project aims to include 132 women in the trial, 66 in the treatment arm and 66 in the control arm

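### The planned random effects for sub parish and participant cancel out of the treatment-by-time interaction, so the test of the intervention effect is not adjusted for sub-parish differences in change, although only six sub parishes are randomised.

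*Protocol article*

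**What the plan says.** The Protocol article, under Data analysis, states the model. Fixed effects are time (baseline, end of intervention, end of follow-up), treatment and their interaction, "as well as age will be specified as fixed effects, and sub parishes and participants as random factors". The section says of the multilevel approach: "Using this technique, regression coefficients will be adjusted for the clustering of observations within sub parishes". It also says: "We will define two levels in our multi-level analysis: (1) participant and (2) sub parishes". No sub-parish-by-time term, random slope or method for degrees of freedom is named. The threshold is "p < 0.05 will be considered significant in all analyses".

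Under Study design, setting and timing, and under Randomization, the six sub parishes are allocated 1:1, so three per arm. The treatment arm has group sessions, for which "each group will be limited to a maximum of 14 members". The control arm receives the infographics at an awareness session.

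Under Sample size calculation, the ICC used is 0.001. The article says that no ICC data for waist circumference exist for Kampala communities and cites a range of 0.001 to 0.10.

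**The concern.** The model is meant to assess changes between arms, so the effect of interest is the treatment-by-time interaction, a contrast within women. A random intercept for sub parish shifts all of its women's measurements by the same amount at every visit. A random intercept for participant does the same for one woman. Both disappear when a later visit is compared with baseline. The interaction is then judged against the visit-level residual alone.

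If women in the same sub parish tend to change together, the six sub-parish mean changes vary more than that residual implies, and nothing in the stated model captures the excess. The promise of adjustment for clustering then fails for the coefficient that answers the trial's question. A Kenward-Roger correction applied to the stated model would not repair this, because it cannot restore a variance component that the model lacks.

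The same model serves waist circumference and the secondary outcomes. The risk is a significant result, with too narrow a confidence interval, that reflects ordinary differences among six communities.

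**Working it through.** **Inputs from the article.** "1.96 at the type 1 error of 5% = 0.842 at 80% power"; "the standard deviation of waist circumference for women aged 18 to 49 years = 13.73" (cm); "effect size = 7.4cm"; cluster size 27 and ICC 0.001 in the design effect; 55 women per arm, raised to 66, 132 in total; six sub parishes, three per arm; three visits.

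**The article's own figure.** m = (1.96 + 0.842)² × 2 × 13.73² / 7.4² × (1 + 26 × 0.001) = 54.06 × 1.026 = 55.46. The article states 55, which agrees to rounding. 55 × 1.2 = 66 and 2 × 66 = 132 are exact. The article gives no type I error for the interaction test other than the nominal 5%.

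**Cluster sizes.** 132 / 6 = 22 women recruited per sub parish; 55 / 3 ≈ 18 after dropout.

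**Degrees of freedom implied by the stated model.** 132 × 3 = 396 measurements. Removing 1 + 131 for participant means, 2 for time and 2 for the interaction leaves 260. Between sub parishes within arms there are 6 − 2 = 4. The figure of 260 follows from the model as written; the article does not state it.

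**Type I error when variation in change is omitted.** Let ρ be the ICC of change (an assumption; not in the article) and n the women per sub parish. The variance of the estimated effect is too small by the factor DE = 1 + (n − 1)ρ, so the true error is 2 × [1 − Φ(1.96 / √DE)].

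Examples: n = 18, ρ = 0.05 gives DE = 1.85, 1.96 / √1.85 = 1.441, error 15.0%. n = 22, ρ = 0.10 gives DE = 3.10, 1.96 / √3.10 = 1.113, error 26.6%.

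| ρ (both arms) | n = 18: formula / simulated | n = 22: formula / simulated |
|---|---|---|
| 0.001 | 5.2% / 5.2% | 5.2% / 5.3% |
| 0.01 | 7.0% / 7.3% | 7.5% / 7.5% |
| 0.05 | 15.0% / 15.4% | 17.1% / 17.4% |
| 0.10 | 23.3% / 23.7% | 26.6% / 27.0% |

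The simulated values come from 20,000 balanced null trials per setting (six clusters, three visits), with the interaction tested against the within-participant residual. In the same trials, a t-test on the six sub-parish mean changes (4 df, critical value 2.776) rejected in 4.7-5.2% at every ρ from 0 to 0.10.

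**If only the treatment arm's changes are correlated.** Averaging over arms, DE = 1 + (n − 1)ρ / 2. At ρ = 0.10:
- Correlation within session groups of 11 (22 women split in two to respect the 14-member cap): DE = 1.50, error 11%.
- Correlation across the sub parish, n = 18: DE = 1.85, error 15%.
- Correlation across the sub parish, n = 22: DE = 2.05, error 17%.

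**Power on 4 df, article's inputs, unadjusted endpoint comparison.** SE = 13.73 × √(2/55 × [1 + (18.33 − 1) × 0.001]) = 2.64 cm, and 7.4 / 2.64 = 2.80. Against 1.96 the power is 80%. Against 2.776, with a non-central t on 4 df, it is about 56%.

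**The case against.** The strongest reply has four parts.

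1. **Intercepts-only is an inference.** The article names random factors without saying that only intercepts are meant, and gives no df method. A full analysis plan, not shown, may add both. What stands: the df are open, so the 260 is only what the stated model implies. But the random part is specified, and a claim of adjustment is attached to it. On its plain reading, that part does not deliver the claim for the interaction, and most of the inflation comes from the missing variance term rather than the df.

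2. **The inflation may be nil.** A reader might infer that type I error will be 15-27%. The article does not support that. Its range of 0.001 to 0.10 concerns waist circumference, not change in it, and at the adopted 0.001, applied to change, the error is about 5.2%. This stands in full: the inflation is conditional. Equally, the article has no data to show that the ICC of change is near zero.

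3. **The mechanism is weaker than equal correlation in both arms.** Only the treatment arm shares sessions, in groups of at most 14, and one coach moderates them all. This stands and gives the lower figures. Other influences could act in either arm: the groups already exist, and the article values their social cohesion.

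4. **Two levels for three visits.** A reader might infer from "We will define two levels in our multi-level analysis: (1) participant and (2) sub parishes" that repeated visits are treated as independent, which would make the interaction's standard error too large. The same section names participants as a random factor, so that analysis is not planned. The phrase is loose wording and no part of this point.

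**Conclusion.** The point holds in conditional form. As written, the model does not adjust the treatment-by-time interaction for sub-parish variation in change, and the statement that coefficients are adjusted for clustering is not true of that coefficient. The true error of the nominal 5% test runs from about 5% to about 27% over ICCs of change of 0.001 to 0.10. This assumes 18 to 22 women per sub parish, equal correlation in both arms, and a range borrowed from the article's figure for waist circumference itself. At an ICC of 0.10 confined to the treatment arm, it is about 11-17%. If sub parishes do not differ in change, there is no inflation. With three sub parishes per arm and no local data on this correlation, the primary test should not depend on its being negligible.

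**What to change.** Add a sub-parish-by-time random effect to the stated model and test treatment by time with a small-sample method (Kenward-Roger or Satterthwaite), which gives about 4 df for the change between two visits. Alternatively, compute the mean adjusted change in waist circumference for each of the six sub parishes and compare the arms by a t-test on 4 df. Either is defensible, and which one is primary is the sponsor's choice. State it in advance, together with what happens if the added variance is estimated as zero, since six clusters make that likely enough to need a rule.

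The change affects analysis wording and a few lines of R; design and conduct are untouched. The cost is wider intervals (critical value 2.776 instead of 1.96) and less power than the stated 80%: about 56% on the article's inputs for an unadjusted endpoint comparison. Baseline adjustment would recover part of this, by an amount that cannot be computed from the article. The power statement should be revised to match the chosen test.

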“Through education sessions, like you come in this group and give us a health talk, like the way you have come, you teach us and then us we can go and teach our other friends out there. Like for us every Tuesday we be meeting here, very many of us, so if you say you will give us one Tuesday in a week or month, or the last Tuesday of a month and you come and teach us”. “It would be very nice, because literally I share the information with others, so it will move, it moves much faster, because these groups are not only here, but also have these groups in other dioceses, so we can go visit them, and the teach them, but in health centers you only visit when you’re sick”. “Yes it helps, what I know is good, I wish it for my friends and we act as a support for each, and we as well spread it to other groups, example of myself, I used to never eat pumpkin, but I got it from these ladies, that this pumpkin is good and with time I gradually started to eat it until it become part of my diet”, participants in FGD 4 and 6.

Additionally, a recent systematic review shows that diet and PA interventions delivered through group sessions are effective in promoting clinically relevant weight loss [34]. These groups provide opportunities for social support, experience sharing, and may create a motivating atmosphere [22, 34]. Our needs assessment as well revealed that the community and church small groups are an opportunity to share dietary and PA counselling [16, 17]. Our environmental asset assessment revealed existence of women groups within religious structures. Existing groups boosts social cohesion, a facilitator for behavioural change [22].

The reading culture of Ugandans is low.

“We need more of practical, and also the pamphlet, some of us don’t really understand so much, but if it brings out the picture very well, even I can pick interest in it”. “Pamphlets, some people are lazy to read”, participants in FGD 5.

So, the BCT of “providing information through imagery” was translated into infographics with less text and more locally recognisable visuals. Evidence as well shows that visuals increase attention, interest, and credibility of the messages [20].

During FGDs with the target group, participants emphasised the need for practical vegetable preparation skills.

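### The planned model puts no cluster term on change over time, so change shared within session groups or sub parishes makes the standard error of the time-by-treatment effect too small

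*Protocol article*

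**What the plan says.** The six sub parishes are randomised 1:1 (protocol article, Randomization). The treatment arm receives infographics and face-to-face sessions; the control arm receives infographics only, handed out at an awareness session (Study design, setting and timing). Sessions run in women's groups that already exist inside the sub parishes: "For the intervention purposes, each group will be limited to a maximum of 14 members". Step III explains why groups were chosen: "These groups provide opportunities for social support, experience sharing, and may create a motivating atmosphere". Step V adds group leaders as peer opinion leaders.

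On numbers: "Hence, the project aims to include 132 women in the trial, 66 in the treatment arm and 66 in the control arm" (Sample size calculation).

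On analysis: "We will define two levels in our multi-level analysis: (1) participant and (2) sub parishes". The linear mixed model has time, treatment, their interaction and age as fixed effects, and sub parish and participant as the random factors. No random term that varies with time is named for any cluster, and no cluster-level test of change is planned.

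**The concern.** The effect of interest is a difference between arms in change from baseline. Change has its own clustering. Women who attend five sessions together, with one leader and mutual support, will tend to change together, and so may women of one sub parish who share local conditions between visits. A random intercept for sub parish describes how sub parishes differ in level at every visit. It says nothing about whether they differ in how much they change.

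If shared change is treated as independent, confidence intervals for the interaction are too narrow and false-positive findings become more frequent. The risk is likely to be greatest for the outcomes the groups work on directly: fruit and vegetable intake, physical activity and food literacy. It applies to waist circumference, the primary outcome, as well.

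**Working it through.** **Inputs from the protocol article.** Table 3: "1.96 at the type 1 error of 5% = 0.842 at 80% power"; "the standard deviation of waist circumference for women aged 18 to 49 years = 13.73"; "effect size = 7.4cm"; "For our intervention, n = 27"; ICC 0.001; 66 women per arm after the dropout allowance. Study design: six sub parishes, groups of at most 14.

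**The plan's own figure.** (1.96 + 0.842)² × 2 × 13.73² / 7.4² = 54.06. Multiplied by 1 + 26 × 0.001 = 1.026, this gives 55.46, which the plan takes as 55. Then 55 × 1.2 = 66. The stated figures are reproduced. They are not the fault here.

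**Number of session groups.** 66/14 = 4.7, so the treatment arm needs at least five. With 132/6 = 22 women per sub parish, 22/14 = 1.6, so an even split gives two groups of 11 in each of three sub parishes, six in all. (Table 3 uses 27 per cluster rather than 22; 27/14 = 1.9 also means two groups.)

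**Why the intercepts drop out.** Write a woman's outcome as sub-parish intercept + person intercept + fixed effects + residual. Her change between two visits contains neither intercept. The model therefore gives the interaction the standard error it would have if all 132 changes were independent.

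**Size, in closed form.** Let D be the mean over the two arms of the true variance inflation of the arm's mean change. The real error rate of a nominal 5% test is 2 × [1 − Φ(1.96/√D)]. The ICC of change is an assumption; the documents do not give one.

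| Shared change | Inflation: treatment, control | D | Error rate |
|---|---|---|---|
| Session group, ICC 0.01, treatment arm only | 1 + 10 × 0.01 = 1.1; 1 | 1.05 | 5.6% |
| Session group, ICC 0.05, treatment arm only | 1.5; 1 | 1.25 | 8.0% |
| Session group, ICC 0.10, treatment arm only | 2.0; 1 | 1.50 | 11.0% |
| Sub parish, ICC 0.05, both arms, no group effect | 1 + 21 × 0.05 = 2.05; 2.05 | 2.05 | 17.1% |

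**Check by simulating change scores** (40,000 runs per row; 3 sub parishes × 2 groups × 11 women per arm; no true effect). The columns compare three analyses: all women independent, groups as the independent units (t, 10 df), and sub-parish means as the units (t, 4 df).

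| Shared change | Women independent | Groups as units | Sub-parish means |
|---|---|---|---|
| Group 0.01, treatment arm | 5.8% | 4.9% | 5.0% |
| Group 0.05, treatment arm | 8.1% | 5.2% | 5.2% |
| Group 0.10, treatment arm | 11.3% | 5.2% | 5.2% |
| Sub parish 0.05, both arms | 17.9% | 10.1% | 5.0% |
| Group 0.05 (treatment arm) plus sub parish 0.05 | 20.4% | 9.2% | 5.0% |

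Only the sub-parish analysis holds its level in every row. It does so with 4 degrees of freedom; with the normal critical value of 1.96 the same test rejects about 12%.

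**Check in the three-visit mixed model** (further assumptions: within-person correlation 0.8, sub-parish share of between-person variance 0.01; group ICC of change 0.10 in the treatment arm).

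- Random intercepts only: the interaction's true standard deviation is 1.88 cm, the model's standard error 1.53 cm, and rejection 10.7%.
- Adding a session-group random intercept leaves the standard error at 1.52 cm, so it cures nothing.
- Adding a sub-parish-by-time term, with no group level, gives 1.88 cm and 5.2%.

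**The case against.** **Groups are nested in the randomised units.** A reader might infer that leaving out a session-group level is in itself what makes the standard errors too small. The documents do not support that. The groups lie inside the sub parishes, so any analysis that handles sub parish at the level of the tested effect already carries the group variance, as the last column of the simulation table shows. The understatement also arises with no group effect at all. This objection stands, and it is why the point is about the missing cluster term on change.

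**Control-arm groups.** A reader might also infer that there are at least five session groups in each arm. Sessions are held in the treatment arm only, and the number and size of any control-arm groups are not given, so no error rate is claimed here for group clustering in both arms.

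**Comparison with Table 3.** It is tempting to set a group design effect of 1.5 against the plan's 1.026. That gap comes from assuming an ICC of 0.05 instead of 0.001. At 0.001, groups of 11 give 1 + 10 × 0.001 = 1.01, which is below 1.026. The comparison says nothing about the number of levels.

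**Condensed wording.** The article does not say that the random factors are intercepts only, and a fuller plan may contain a time-varying term. This is fair and limits confidence. But the article does list the levels and the random factors, and none of them acts on change.

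**The ICC is assumed.** If change were as weakly clustered as the 0.001 in Table 3, the effect would be negligible: D = 1 + 21 × 0.001 = 1.021 for sub parishes, an error rate of about 5.2%. Nothing in the document shows that change is so weakly clustered in an intervention built on group influence.

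**Conclusion.** The concern holds in this form: as written, the model tests a time-by-treatment interaction with no cluster term acting on change, and its standard error is too small whenever women in a session group or a sub parish change together. The direction does not depend on the assumed values; the size does. Under an even split into two groups of 11 per sub parish, a nominal 5% test rejects about 6%, 8% and 11% at a group ICC of change of 0.01, 0.05 and 0.10 in the treatment arm alone, and about 17-18% at a sub-parish ICC of change of 0.05. Confidence is medium, because the article may condense a fuller specification. The plan should be changed.

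**What to change.** 1. Base the primary test on the sub-parish mean changes, or add a sub-parish-by-time random term to the mixed model. In either case state small-sample degrees of freedom (about 4 from six clusters). Both options carry the session-group variance.
2. Record each woman's group at enrolment. As a secondary step, add a group-by-time random term nested within sub parish, in the treatment arm, or in both arms if control women belong to recorded groups. Report the group ICC of change.
3. Do not rely on a group random intercept, or on a group-by-time term without the sub-parish-by-time term. The first leaves the standard error unchanged; the second treats groups as the independent units and still rejects about 9-10% if sub parishes share change at an ICC of 0.05.

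The cost is one identifier in the database and a revised random structure. The downside is real: with 4 degrees of freedom the critical value is 2.776 instead of 1.96, so intervals are about 42% wider (2.776/1.96 = 1.42) before any increase in the standard error, and variance components from six clusters will be imprecise.

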### Outcomes

Primary outcome is reduction in waist circumference. Decreases in waist circumference are recommended as critically important treatment target for reducing adverse cardiometabolic health risks [15]. Secondary outcomes include optimisation of, fasting blood glucose, total cholesterol, HDL, LDL, triglycerides, body composition, food literacy, PA, and fruit and vegetable intake.

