Fourth, the intervention is designed with a combination of eleven evidence based BCT, scientifically proven to enact changes in knowledge, skills, self-efficacy, subjective norms, and social support to create a sustainable behaviour change [20, 35, 36, 43]. The limitation is that the evidence for the effectiveness of the BCT is exclusively from HIC due to lack of evidence in urban SSA. Questions may be raised on the applicability and effectiveness of scientifically proven BCT in HIC in urban SSA. Theoretically, scientifically proven BCT in the HIC, could positively influence behaviour change in other settings provided they are translated into practical strategies with critical consideration of parameters of use documented by Eldredge, Markham [20]. In our intervention, we carefully considered the parameters of use suggested by Eldredge, Markham [20]. If successful, the intervention could contribute evidence on the validity/applicability of scientifically proven BCT in High Income Countries in urban SSA and how they can be translated.

Fifth, our intervention equips participants with skills and self-efficacy to evaluate nutrition information. Studies show that over the last decade, the virtual environment has become an important determinant of dietary and PA behaviour [46]. A lot of nutrition information is shared on social and mass media, yet majority of the public lacks the skill and self-efficacy to distinguish between factual and non-factual nutrition information. Lastly, in our evaluation design of the intervention, we have included a post intervention follow-up measurement moment. This allows us to analyse the long-lasting effect of the intervention.

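### The stated time comparisons omit the between-arm month-6-versus-baseline contrast that the durability aim needs, and no month or contrast is named as deciding the primary outcome

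*Protocol article*

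**What the plan says.** All references are to the protocol article.

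- **Outcomes:** "Primary outcome is reduction in waist circumference". No month is attached.
- **Study design, setting and timing:** "The study period is divided into two phases: a three-month intervention and a three-month post-intervention follow-up phase". Table 4 has waist measured at baseline (M1), at the end of the intervention (M2, month 3) and at the end of follow-up (M3, month 6).
- **Data analysis, comparisons:** "end line measurement (M_2_) will be compared with base-line measurement (M_1_) and post-follow up measurement (M_3". M3 against M1 is not in the list.
- **Data analysis, model:** besides time, "treatment (and interaction of time and treatment) as well as age will be specified as fixed effects", with sub parish and participant as random factors.
- **Data analysis, error control:** "p < 0.05 will be considered significant in all analyses". Adjustment is confined to post hoc work: "Tukey or Benjamini–Hochberg procedures will be applied when performing post hoc analyses to further identify differences within treatments as well as between time points".
- **Discussion, on the follow-up visit:** "This allows us to analyse the long-lasting effect of the intervention".
- **Sample size calculation:** one comparison, with "1.96 at the type 1 error of 5% = 0.842 at 80% power" and no month given for the 7.4 cm effect.

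**The concern.** There are two linked problems.

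**The stated contrasts do not match the stated purpose.** The effect that lasts to month 6 is the arm difference in change from M1 to M3. The listed M2-versus-M3 comparison asks something else: whether the effect moved after the sessions ended. Failing to find movement is not evidence that the benefit held. A report built on the listed contrasts could present a non-significant M3-versus-M2 interaction as maintenance.

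**The deciding test is open.** Three visits and a treatment-by-time interaction give more than one estimate that could be called a reduction in waist circumference. None is named, and each would be read at 0.05. The choice between month 3 and month 6 could then be made after the results are known.

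A smaller matter concerns precision. With a free treatment main effect and M1 among the outcomes, the arms may differ at baseline in the model. The interaction is then a plain difference of changes and does not use the baseline value as efficiently as it could.

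**Working it through.** **1. The plan's own figure.** Inputs from Table 3: z-values 1.96 and 0.842, SD 13.73 cm, effect 7.4 cm, cluster size 27, intra-cluster correlation 0.001.

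- (1.96 + 0.842)² × 2 × 13.73² / 7.4² = 54.06
- Design effect 1 + 26 × 0.001 = 1.026
- 54.06 × 1.026 = 55.46 (stated as 55), and 55 × 1.2 = 66 per arm

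The figure is reproduced. It covers one test at two-sided 0.05.

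**2. What the model contains.** Let D1, D2 and D3 be the arm differences at the three visits. With M2 as reference, the two interaction coefficients are b1 = D1 − D2 and b3 = D3 − D2. The durability contrast is D3 − D1 = b3 − b1. It is estimable but is neither of the two listed comparisons. The treatment main effect under this coding is D2, the raw arm difference at month 3.

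**3. Why D3 − D2 is a poor guide to durability.** This illustration uses SD 13.73, 55 per arm, no clustering, and an assumed between-visit correlation r that the article does not give. The SE of the difference in change is 13.73 × √(2(1 − r)) × √(2/55). The detectable difference is 2.802 × SE.

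| r (assumed) | SE (cm) | Detectable at 80% power (cm) | Power if 1.5 cm is lost |
|---|---|---|---|
| 0.7 | 2.03 | 5.7 | 11% |
| 0.8 | 1.66 | 4.6 | 15% |
| 0.9 | 1.17 | 3.3 | 25% |

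The 1.5 cm stands for losing half of a supposed 3 cm month-3 effect. Such a loss would usually go unseen.

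**4. False-positive chance if either month may count.** Take D2 − D1 and D3 − D1, each tested at two-sided 0.05. If the three visits are equally correlated (assumed), each contrast has variance 2v(1 − ρ) and their covariance is v(1 − ρ), so they correlate at 0.5.

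- Independent tests (ceiling): 1 − 0.95² = 0.0975
- Correlation 0.5: 0.091
- Absolute correlation 0.9: 0.070
- Counting only waist reductions, correlation 0.5: 0.045, against 0.025 for a single test

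**5. Splitting alpha instead.** At 0.025 for each month, the formula in step 1 gives 67.1, so 68 per arm before dropout (68 × 1.2 = 81.6, so 82 with the plan's own inflation). At 55 per arm, power falls from 79.7% to 70.8%.

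**6. Use of baseline.** The variance of a baseline-adjusted contrast relative to a change-score contrast is (1 − r²) / (2(1 − r)) = (1 + r)/2. This is 0.95 at r = 0.9 (assumed for waist) and 0.75 at r = 0.5 (assumed for noisier outcomes). The formula is at participant level and takes no account of the six clusters.

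**The case against.** The strongest reply is that nothing is lost. All three visits are in one model, changing the reference visit only re-parameterises it, and the post hoc comparisons between time points could include M3 versus M1, since Tukey is an all-pairs procedure. This stands against one tempting inference, that the month-6-versus-baseline effect is never tested. The documents do not support that reading; the contrast is available but not pre-specified. The reply does not remove the mismatch, because the post hoc sentence does not name the between-arm month-6 contrast and leaves the type of error control open.

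A reader might also infer that either listed comparison could carry the primary claim. It could not: only M2 versus M1 measures reduction from baseline. The real ambiguity is between month 3 and month 6, each against baseline.

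Nor can it be said that the M3-versus-M2 interaction is bound to be non-significant. The article gives no within-person correlation. On the assumptions of step 3, a loss of half of 7.4 cm (3.7 cm) would be detected with 45% power at r = 0.7 and 89% at r = 0.9.

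Finally, a condensed article may leave the order of testing to an analysis plan that is not shown, and calling M2 the end line measurement points towards month 3. Both are fair. But the article itself chose to state the contrasts, and the set it states does not serve the aim it gives for the follow-up visit. A model with a free baseline difference is also valid, so the efficiency point is a preference with little effect on waist.

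**Conclusion.** The point holds as an omission and an ambiguity that should be corrected; it does not make the trial unable to study durability. The stated comparisons leave out the between-arm M3-versus-M1 contrast, and neither the Outcomes nor the Data analysis section fixes which month or contrast decides the primary outcome.

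If both months against baseline could count, the false-positive chance is about 0.09 two-sided, or 0.045 against 0.025 in the direction of benefit. A flat 10% would overstate this, since 0.0975 is the ceiling under independence. These figures assume equally correlated visits and that each test holds its nominal level. They apply only if a claim would in fact be accepted from either month. The weak power of M3 versus M2 to reveal a partial loss also rests on assumed correlations.

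**What to change.** 1. Use M1 as the reference visit.
2. Name treatment by M2 versus M1 for waist circumference as the single primary contrast, in line with M2 being the end-line visit.
3. Pre-specify treatment by M3 versus M1 as the key secondary durability contrast, tested only if the primary is significant.
4. Report M3 versus M2 descriptively, with its confidence interval, and do not read non-significance as maintenance.
5. As a secondary improvement, constrain the arm means to be equal at M1 or adjust for each woman's baseline value. Expect little gain for waist and more for noisier outcomes.

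This changes analysis wording only. With one primary test, the stated 55 (66 with dropout) per arm stands on the article's own inputs, whereas keeping both months as primary would need the larger sample in step 5 of the working. The downside is that success could not be claimed from month 6 alone. If an analysis plan already fixes the month and the contrast, the article should be reconciled with it.
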